### Daily spontaneous breathing trial (SBT) assessment/performance for both groups

Prior to the start of a SBT the patient should demonstrate: (1) a partial reversal of the underlying cause of ARF, (2) SpO_2_ ≥ 88 % or PaO_2_ ≥ 55 mmHg with FiO_2_ ≤ 0.40 and PEEP of 8 cmH_2_O or less, (3) hemodynamic stability, (4) a level of sedation appropriate for SBT, and (5) the ability to spontaneously breathe.

The SBT will be conducted for 30 to 60 min. The SBT should be conducted while attached to the ventilator with the ventilator set at zero or 5 cmH_2_O pressure support and zero or 5 cmH_2_O of CPAP or via a T-piece with the same FiO_2_ as during ventilation. Any of the following criteria identify failure of the SBT: (1) respiratory rate (RR) ≥ 35/min for 5 min or longer, (2) sustained SpO_2_ < 88 %, (3) mean arterial pressure sustained < 60 or > 120 mmHg, (4) ischemic changes on the electrocardiogram, (5) new onset of paradoxical breathing, accessory muscle use, nasal flaring, etc., and (6) agitation, diaphoresis, anxiety that does not resolve with reassurance. Those patients successfully completing a 30- to 60-min SBT will be extubated unless there is a specific reason not to extubate. The reason for not extubating a patient after a successful SBT will be documented.

### General care and procedures for both groups of patients

All participating patients, regardless of the study arm into which they are randomized, will be monitored and managed following general standard of care practices aimed at maintaining optimal conditions. Measurement of auto-PEEP (the static end-expiratory pressure following an end-expiratory pause of at least 2.0 s) and measurement of plateau pressure (the static end-inspiratory pressure following an end-inspiratory pause of at least 2.0 s) will be performed daily as needed. Active humidification or heat and moisture exchangers (HMEs) may be used on patients on either group. Mechanical dead space will be minimized on all patients. Use of inline suction catheters is up to the discretion of the investigator; however, they are recommended in all patients. Normal body temperature will be maintained. Ventilator circuits and inline suction catheters do not need to be changed on a regular basis. During airway suctioning the following will be avoided: instillation of saline, manual ventilation, and aggressive suction. Suctioning will only occur when secretions are present; routine suctioning should be avoided. Ideally metered-dose inhalers (MDIs) or Aerogen nebulizers should be used for aerosol therapy. A spacer should be maintained in the inspiratory limb. If a small volume nebulizer is used, a one-way valve T-piece will be used to avoid disconnection of the circuit. Correction for compressible volume of the circuit will be activated in all patients regardless of arm of the study.

Minimal sedation and appropriate analgesia will be maintained in all patients. The sedative/analgesic regimen and dose will be those selected by the managing physician at all times according to the needs of the patient and unit policies. Sedation should be titrated according to any of the commonly used sedation scales: the Riker Sedation-Agitation Scale (SAS) [19], the Ramsay Sedation Scale [20], or the Richmond Agitation Scale (RASS) score [21] (see Additional file 4). Appropriate analgesia will be given so that no more than minimal sedation will be necessary. The specific drugs used and dosing regimen will be left up to the individual investigator. Drugs used and dose per kg will be recorded on the data forms.

When an appropriate fluid challenge fails to restore adequate blood pressure and organ perfusion, therapy with vasopressor agents should be started. Either norepinephrine or dopamine (through a central catheter as soon as available) is the first-choice vasopressor agent to correct hypotension in septic shock. Vasopressin may be considered in patients with refractory shock despite adequate fluid resuscitation and high-dose conventional vasopressors. These recommendations may be revised as the new surviving sepsis guidelines become available. In patients with low cardiac output despite adequate fluid resuscitation, dobutamine may be used to increase cardiac output. If used in the presence of low blood pressure it should be combined with vasopressor therapy. A strategy of increasing Cardiac Index to achieve an arbitrarily predefined elevated level is not recommended.

Enteral nutrition should be provided as soon as it is deemed safe by the treating physicians. Exogenous insulin should be provided with the goal of achieving a blood glucose level below 150 mg/dl for the first 3 days of critical illness. If, after 3 days, enteral nutrition has been established and other resuscitation measures have been provided, a goal of normoglycemia (110–140 mg/dl) should be considered. This approach should minimize the potential impact of hypoglycemia. Ongoing randomized controlled trials may change these recommendations, in which case we will provide protocol amendments if necessary.

Data on lung mechanics, gas exchange, and hemodynamics will be gathered before applying study settings, then after applying study settings at times 0, 4 h, 24 h, 48 h, 96 h, 7 days, 10 days, 14 days, and every 7 days thereafter and on the last day of invasive ventilatory support (Table 1). At initiation of the protocol and at 4 h, data collected will represent one point in time, that is individual data will be coupled. However, each day after that data will not be coupled since the highest and lowest value for each variable will be recorded. It is expected that this data will be collected between 8 a.m. and 12 noon each day. Also, at this time the maximum Edi (the peak inspiratory value) will be reassessed and readjustments of MV will be made if necessary. Patients will be followed-up (alive or dead) until ICU discharge. In addition, we will record hospital length of stay and mortality.

**Table 1 Tab1:** Schedule of events

Events	Screening Day	Randomization (Day 0)	Day 1	Day 2	Day 3	Day 7	Day 10	Last day on MV
Study procedures								
Informed consent form	X							
Medical history	X	X	X	X	X	X	X	X
Demographics	X							
Intervention								
Treatment/intervention		X	X	X	X	X	X	X
Blood chemistry								
Blood gases	X	X	X	X	X	X	X	X
Efficacy measure								
Lung mechanics	X	X	X	X	X	X	X	X
NAVA levels	X	X	X	X	X	X	X	X
Hemodynamic data	X	X	X	X	X	X	X	X
Radiological tests								
Chest X-ray	X	X	X	X	X	X	X	X

*MV* mechanical ventilation, *NAVA* Neurally Adjusted Ventilatory Assist

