## Methods/design

### Justification of the study

Patient-ventilator asynchrony is a common problem in mechanically ventilated patients with ARF who are receiving assisted ventilation. Based on new data, all patients managed with conventional modes of MV have an AI > 5 % at various points during the day [3]. NAVA is a unique approach to MV based on neural respiratory output, providing a smooth transition to natural breathing. NAVA better assures that the patient’s breathing is in synchrony with, and in proportion to, the patient’s own efforts, regardless of patient category or size.

We justify the need for our study based on the fact that NAVA can provide a smooth transition to natural breathing. We hypothesized that the use of NAVA compared to conventional lung-protective MV will result in a decrease in the number of days of MV. It is further hypothesized that NAVA will result in a decrease in the length of ICU and hospital stay. The goal of this study is to compare the ability of NAVA versus conventional lung-protective MV to provide invasive ventilatory support during ARF in adults who are expected to require ventilatory support for at least 72 h.

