**Fig. 1 Fig1:**
[figure not shown]
Study design diagram

The randomization list was done by the statistician of the study ([name]), according to a computer-generated random number table based on a 1:1 allocation. This list was generated when the investigators and all Ethics Committees and IRBs of the participating centers had approved the study design. Randomization is stratified by center to ensure an equal distribution of patients in each arm by each ICU. Patients are randomly allocated to the two arms of the study (NAVA or no NAVA) by the clinical investigator in each participating ICU according to the precise written allocation contained inside a prenumbered, opaque, sealed envelope sent in blocks of ten envelopes to each participating ICU. Investigators must respect the numerical sequence of the envelopes. Only two members of the Trial Management Team have access to the randomization list: the project manager and the statistician. They keep the randomization list in their private office at the Research Unit of the Coordinating Center. The coordinating center does not enroll patients.

Our study characteristics do not allow the blinding of investigators to the intervention being tested. Once a participating ICU randomizes a patient, their investigators must contact the project manager of the study to inform and confirm the randomization number, the correct sequence of the prenumbered envelope, and the intervention arm. Screening, enrollment, randomization, treatment initiation, and follow-up of randomized patients is performed by the investigators and attending physicians in each participating ICU. Subsequent blocks of ten envelopes are sent to those participating ICUs with high enrollment rates. Participating clinicians do not know whether the pattern of stratification by center is for every 10, 20, or more envelopes during the study period.

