### Primary and secondary outcomes

The primary outcome of interest is the number of VFDs, defined as days alive and free from MV at day 28 from the onset of MV and from the day of randomization. For subjects ventilated for 28 days or more and for subjects who die, VFDs is 0. The secondary outcomes of interest include: length of invasive MV, length of post-extubation noninvasive ventilation, total assisted VFDs (invasive plus noninvasive), length of ICU and hospital stay, and ICU and hospital mortality, development of extrapulmonary organ failure (any organ failure developed during the study that was not present at the time of enrollment into the study) [22], prevalence of barotrauma (defined as the presence of any extrapulmonary air that was not present at study enrollment), ventilator-associated pneumonia (development of a pneumonia 48 h after study entry), development of ARDS after enrollment into the study, as defined by the American-European Consensus Conference (AECC) criteria for ARDS [23] or as moderate/severe ARDS by the Berlin criteria [17], and time from first SBT to extubation.

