### Sample size calculations and interim analysis

It is anticipated that the average patient with asynchrony who is enrolled into this trial will have 21 VFDs with a standard deviation (SD) of 6 VFDs, based on data from Wit et al. [2]. Considering the impact of improved synchrony on length of MV, we anticipate that NAVA will increase VFDs by 2 days. No patient loss has been considered. We will only analyze patients who are enrolled and randomized. The power analysis has been performed according to Schoenfeld et al. [24]. Thus, the sample size with an alpha of 0.05 and a beta of 0.2 (80 % power) is 153 patients in each group or a total of 306 patients requiring randomization.

Interim analysis will be performed at hospital discharge of the first 102 and 204 randomized patients. If, at the time of these analyses, there is a trend toward better outcome in the control group (*p* < 0.1) the study will be terminated. The study will continue to randomize 306 patients if no adverse impact of the NAVA group is observed. The interim analysis will be performed at the coordinating center (Hospital Universitario [name], Las Palmas de Gran Canaria, Spain) by an independent Data and Safety Monitoring Board (DSMB). It is expected that DSMB meetings will be by conference call and DSMB discussions by email or conference call.

All adverse events reported will be sent to the DSMB as well as to the IRB for review (see Additional file 4). All serious events will be sent within 24 h after being received by the coordinating center. Nonserious events will be sent within 1 week of reception by the coordinating center. All unexpected, and related or possibly related, adverse events will be reported to the DSMB and the IRB. The DSMB will review the overall status of the study: number of patients enrolled overall and in each center, adherence to the protocol overall and by each center.

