### Data analysis

Data will be collected in each participating ICU using a standardized form. Data will be transmitted to the coordinating center whenever a patient dies or is discharged from the hospital. Before exporting the data into a computerized data base at the coordinating center, a trained data collector from the coordinating center will check the completeness and the quality of information. Logical checks will be performed for missing data and to find inconsistencies, especially regarding clinical diagnosis, date, and ventilatory parameters. If necessary, the data collector will contact the investigator by phone to validate the data or reformat the data for entry into the database.

Descriptive statistics will be expressed as mean ± SD or median and interquartile range depending on the nature and distribution of the variables. Inferential statistics will use estimates of the mean of the differences and their 95 % confidence intervals (CI). Variables normally distributed will be compared with the Student’s *t* test. For variables without a normal distribution, the Mann-Whitney *U* rank test will be used for comparison. Categorical variables will be compared using Fisher’s exact test. The primary outcome variable (number of VFDs) will be assessed with the Student’s *t* test or the Mann-Whitney *U* rank test dependent on the distribution of the data. The relative risks and their 95 % CIs will be estimated. For all these comparisons, we will consider a difference to be statistically significant if *p* < 0.05.

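### Ventilator-free days are a day-28 outcome, but the zero score for death has no time limit and vital status is observed only to hospital discharge

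*Protocol article*

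**What the plan says.** All places are in the protocol article, under Methods/design.

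- **Outcome** (Primary and secondary outcomes): VFDs are "days alive and free from MV at day 28 from the onset of MV and from the day of randomization". The abstract names only intubation as the starting point.
- **Zero rule** (same section): "For subjects ventilated for 28 days or more and for subjects who die, VFDs is 0". No limit on the time of death is attached.
- **Follow-up** (General care and procedures for both groups of patients): "Patients will be followed-up (alive or dead) until ICU discharge. In addition, we will record hospital length of stay and mortality".
- **Closing of the record** (Data analysis): "Data will be transmitted to the coordinating center whenever a patient dies or is discharged from the hospital". The interim analyses are likewise timed by hospital discharge (Sample size calculations and interim analysis).
- **Mortality outcomes** (Primary and secondary outcomes): "length of ICU and hospital stay, and ICU and hospital mortality". Day-28 mortality is not listed.
- **Expected effect on stay** (Justification of the study): "It is further hypothesized that NAVA will result in a decrease in the length of ICU and hospital stay".
- **Blinding** (Enrollment into the study and randomization): "Our study characteristics do not allow the blinding of investigators to the intervention being tested".

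**The concern.** A day-28 outcome with death scored 0 needs every patient's vital and ventilation status over the same 28 days. The stated rules tie observation to the length of the hospital stay instead. A patient who leaves hospital alive before day 28 and then dies, or is reintubated elsewhere, keeps a high VFD score because nobody looks.

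If the lost time were the same in both arms, this would mainly add noise. But a shorter hospital stay with NAVA is one of the trial's own hypotheses, and the investigators who manage the patients know the allocation. A shorter stay gives less time in which a death can be seen. With equal true mortality, that lowers the count of deaths under NAVA and raises its mean VFDs. Because the error comes from data never collected, no analysis can repair it afterwards.

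**Working it through.** **1. The window under each reading of the zero rule**

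| Event | Any recorded death scores 0 (literal) | Only deaths by day 28 score 0 | Fixed 28-day window |
|---|---|---|---|
| Extubated day 7, dies in hospital day 45 | 0 | 21 (28 − 7) | 21 |
| Extubated day 7, leaves hospital alive day 12, dies day 20 | 21, death not seen | 21, death not seen | 0 |
| Extubated day 7, leaves hospital day 12, reintubated elsewhere day 20, survives | 21, not seen | 21, not seen | up to 8 days lower (28 − 20) |

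The literal window is the hospital stay. The bounded window is the shorter of the hospital stay and 28 days. Neither is a fixed 28 days, and the second and third rows are wrong under both readings. The third row assumes that VFDs count days off the ventilator.

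**2. Inputs from the sample size section**

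Control patients "will have 21 VFDs with a standard deviation (SD) of 6 VFDs"; the target gain is 2 days, so 23 VFDs with NAVA; 153 patients per arm; alpha 0.05, taken as two-sided; power 80%.

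Check of the plan's figure: n = 2 × (1.960 + 0.842)² × 6² / 2² = 141.3, so 142 per arm, or 143 with the t distribution. Dividing 143 by the Mann-Whitney relative efficiency of 0.955 gives 150, within 3% of the stated 153. The present point does not depend on this number.

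**3. Effect of misclassified patients on the mean difference**

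- One death wrongly scored or wrongly missed moves an arm mean by 21/153 = 0.14 to 23/153 = 0.15 days.
- One missed reintubation on day 20 in a survivor moves it by at most 8/153 = 0.05 days.
- A between-arm difference of 1 percentage point in wrongly counted deaths (about 1.5 patients of 153): 0.01 × 21 = 0.21 days, and 0.21/2 = 10.5% of the target. With 23 VFDs it is 0.23 days.
- A difference of 3 points: 0.03 × 21 = 0.63 days, or 0.69 with 23.
- The standard error with the plan's SD is 6 × √(2/153) = 0.686 days. With no true effect, two-sided rejection would be about 6% at 1 point and 15 to 17% at 3 points.

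The 1-point and 3-point inputs are illustrations. The article gives no discharge times or post-discharge death rates.

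**4. How large a difference might arise**

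Simulation with identical true mortality in both arms, 153 per arm, 1,000 repetitions per scenario. All rates are assumed: 15% early deaths, mean ventilation about 7 days, a death hazard after extubation of 0.002 to 0.006 per day, and a mean hospital stay after extubation of 20 days in control and 12 or 16 days with NAVA.

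| Scoring | Difference in counted deaths | Spurious gain for NAVA | t-test rejection |
|---|---|---|---|
| Any in-hospital death = 0 | 0.7 to 3.4 points | +0.09 to +0.67 days | 5.1 to 8.7% |
| In-hospital deaths by day 28 = 0 | 0.2 to 1.4 points | +0.01 to +0.27 days | 4.5 to 5.2% |
| Fixed 28-day window | about 0 | −0.05 to −0.02 days (noise) | 4.8 to 5.4% |

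The same hazard runs before and after discharge. Patients discharged alive are fitter than that, so missed deaths are probably overstated.

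**The case against.** Several stronger conclusions are tempting, and the article does not support them.

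- **That every death, whenever it occurs, scores 0.** The zero rule directly follows a definition fixed at day 28, and the bounded reading is the more natural one. The day-45 case shows that the wording is loose; it is not evidence of what the investigators will do.
- **That vital status stops at ICU discharge.** The follow-up sentence goes on to hospital mortality, and records close at death or hospital discharge. Only the time after live hospital discharge or transfer is unseen.
- **That each misclassified patient costs about 21 days.** This holds for a death. A survivor reintubated on day 20 loses at most about 8 days.
- **That the primary test is seriously inflated.** Rejection of 15% or more comes from a chosen 3-point difference, not from anything in the article.

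The size argument goes further. Patients are expected to need at least 72 more hours of ventilation, and those with three or more organ failures or a high risk of death within 3 months are excluded. Few may leave hospital and die before day 28. The plan also presents a shorter stay as a consequence of NAVA working, so if NAVA does nothing there is little reason for the windows to differ.

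Finally, an article condenses a fuller protocol, which may contain a day-28 contact. Table 1 schedules measurements during ventilation, so its lack of a day-28 column proves little, and the point does not rely on it.

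All of this limits the size. It does not remove the mismatch: the article is not silent but states where follow-up ends, and that end does not deliver a 28-day window under either reading.

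**Conclusion.** The point holds in limited form. The definition of the primary outcome and the stated end of follow-up do not fit together. Under the more natural reading, what is lost is deaths and reintubations between live hospital discharge or transfer and day 28. The zero rule should also carry its time limit, so that later in-hospital deaths cannot be scored 0.

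A bias towards NAVA is possible because a shorter stay is hypothesised, but the article neither shows it nor allows it to be sized. The conditional figure is about 0.21 days per percentage point of between-arm difference in wrongly counted deaths, roughly a tenth of the planned effect. Under the assumed rates the bounded reading gave at most +0.27 days with almost no change in the rejection rate; the literal reading gave up to +0.67 days with rejection of about 9%. I would call it probably modest and worth correcting because the correction is cheap. If the full protocol already has a day-28 status check, what remains is the wording of the zero rule and of the follow-up sentence.

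**What to change.** 1. Reword the zero rule: VFDs are 0 if the patient dies on or before day 28 or is ventilated through day 28; deaths after day 28 do not change VFDs.
2. Count day 28 from one time origin. The abstract says intubation; the outcomes section names both onset of ventilation and randomization. Since randomization may come up to 5 days after intubation, the two windows can end up to 5 days apart. The sponsor must reconcile these passages and fix the origin; this point does not settle which.
3. For every patient discharged or transferred from hospital before day 28, obtain vital and ventilation status at day 28 by telephone or record check, and amend the follow-up sentence and the rule for closing the record to match.

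The cost is a short amendment, a field on the data form, and one call or record check per patient who leaves hospital before day 28. The sample size stays at 153 per arm.

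### The primary outcome runs to day 28, but stated follow-up ends at ICU discharge, so ventilation status between ICU discharge and day 28 is not provided for

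*Protocol article*

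**What the plan says.** All references are to the protocol article.

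- **Outcome window.** Under *Primary and secondary outcomes*, VFDs are "defined as days alive and free from MV at day 28 from the onset of MV and from the day of randomization". The scoring rule is: "For subjects ventilated for 28 days or more and for subjects who die, VFDs is 0".
- **Follow-up.** Under *General care and procedures for both groups of patients*: "Patients will be followed-up (alive or dead) until ICU discharge. In addition, we will record hospital length of stay and mortality". The second of these sentences lists what is collected beyond ICU discharge. Ventilation is not on the list.
- **Schedule.** The same section and Table 1 place the final measurement on the last day of ventilation. There is no day-28 contact and no check after the ICU.
- **Data flow.** Under *Data analysis*: "Data will be transmitted to the coordinating center whenever a patient dies or is discharged from the hospital". Under *Sample size calculations and interim analysis*: "Interim analysis will be performed at hospital discharge of the first 102 and 204 randomized patients". Both are tied to hospital discharge, not to day 28.
- **Reintubation.** *Ventilatory management* foresees it after extubation. No section says how ventilated days after a first liberation enter the VFD count.

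**The concern.** A VFD count to day 28 is only as good as the knowledge of who was on a ventilator on each of those days. The article states a follow-up end that depends on where the patient is, and for many survivors that end will come well before day 28. Two kinds of patient are exposed: a survivor who is ventilated again after leaving the ICU, and a patient who is moved elsewhere while still ventilated. If those days are not recorded, nothing removes them from the count, because the scoring rule sets VFDs to zero only for death or for 28 or more days of ventilation. Collecting vital status alone would not repair this.

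The error in each arm has one direction: VFDs come out too high. What matters for the trial is whether the arms differ. ICU discharge, which sets the end of follow-up, is itself expected to come earlier under NAVA (*Abstract*, *Background*, *Justification of the study*), and investigators are not blinded. Unequal losses are therefore possible.

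**Working it through.** **1. The windows side by side.**

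| Item | Ends at |
|---|---|
| Primary outcome | Day 28 |
| Stated patient follow-up | ICU discharge |
| Items added after the ICU | Hospital stay and mortality only |
| Scheduled measurements | Last day of ventilation |
| Form sent to coordinating center | Death or hospital discharge |

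No row other than the outcome itself reaches day 28 for a patient who leaves hospital earlier.

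**2. How much of the window is exposed.** The planned mean is 21 VFDs, so 28 − 21 = 7 days are not ventilator-free on average. This mean includes zeros for deaths, so survivors would have fewer than 7. Assume that ICU discharge follows extubation by 2 to 5 days (not in the documents). Then 28 − (7 + 2) = 19 and 28 − (7 + 5) = 16, so about 16 to 19 days of the window fall after ICU discharge for a typical patient.

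**3. Overstatement within an arm.** Mean overstatement = share of patients affected × ventilated days missed per affected patient. The documents give neither input; all values are assumptions.

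- 0.02 × 3 = 0.06 days
- 0.05 × 7 = 0.35 days
- 0.10 × 12 = 1.2 days

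**4. Effect on the difference between arms.** If both arms have the same overstatement, it cancels in the mean difference. If 8% are affected in one arm and 4% in the other (assumption):

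- (0.08 − 0.04) × 7 = 0.28 days; 0.28 / 2 = 14% of the planned effect
- (0.08 − 0.04) × 10 = 0.40 days; 0.40 / 2 = 20% of the planned effect

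**5. Scale against the trial's precision.** The planned figures are a difference of 2, SD 6, 80% power, alpha 0.05 (taken as two-sided) and 153 per arm. The two-sample formula gives 2 × [6 × (1.960 + 0.842) / 2]² ≈ 141.3, so 142 per arm. Dividing by the Mann-Whitney efficiency 3/π gives 149, within 3% of the stated 153. This point does not depend on that figure.

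The standard error of the difference at 153 per arm is 6 × √(2/153) = 0.686 days. A shift of 0.28 to 0.40 days is then 0.41 to 0.58 standard errors.

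If the larger loss were in the control arm, the observed difference would shrink. Power = Φ(difference / 0.686 − 1.96):

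| Observed difference (days) | Power |
|---|---|
| 2.0 | 83.0% |
| 1.9 | 79.1% |
| 1.8 | 74.7% |
| 1.5 | 59.0% |

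If the larger loss were in the NAVA arm, the shift would favor NAVA.

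**The case against.** A reader might infer that the plan stops observing ventilation at ICU discharge, misses every later return to the ventilator, and credits those days as ventilator-free. The documents do not support that reading, for four reasons.

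- The follow-up sentence carries the qualifier alive or dead. It limits vital-status follow-up and does not say that ventilation data stop there.
- The form stays open until death or hospital discharge and is checked for dates and ventilatory parameters before entry. Re-ventilation in the same hospital could be captured.
- The last scheduled measurement is tied to the end of invasive support, not to the ICU. A patient moved while still ventilated has not reached it, so nothing says that this patient is coded as liberated at transfer.
- No section states how unseen days are counted. Crediting them is an inference.

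It can also be said that case report forms and an investigator manual exist (*Trial organization*) but are not shown, and that a journal article may leave counting rules to them.

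These points narrow the concern but do not remove it. If the sentence concerns vital status only, the article states no follow-up window for ventilation at all. An open form is not an instruction to collect an item, and it closes at hospital discharge. Nor is this mere silence: the article names a follow-up end and the items added after it, and together they fall short of its own primary outcome. An analysis plan cannot recover data that were not collected.

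The objection to the size stands in full. Every rate is assumed, including the twofold imbalance, and nothing in the documents shows more failures after the ICU under NAVA.

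**Conclusion.** The point holds as a mismatch between the outcome window and the stated follow-up. Followed as written, the plan can leave ventilated days between ICU discharge and day 28 out of the VFD count. The gap is clearest after hospital discharge or transfer; within the same hospital it may be closed in practice.

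Any missed days overstate VFDs in the arm concerned. Bias in the treatment difference requires unequal misses. That is possible, because NAVA is expected to shorten ICU stay, but it is not shown. The illustrative sizes, 0.06 to 1.2 days within an arm and 0.28 to 0.40 days between arms, rest wholly on assumed shares and durations. They show that the effect could range from negligible to a fifth of the planned 2-day difference; they do not estimate it.

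**What to change.** Amend the follow-up statement in *General care and procedures for both groups of patients* so that invasive ventilation status is recorded to day 28 for every randomized patient regardless of location. This covers the time after ICU discharge, hospital discharge and transfer. Record the dates of any new or continuing invasive ventilation. State in *Primary and secondary outcomes* that VFDs are derived from all ventilated days to day 28.

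The cost is one case-report item, a few calls to receiving units and a short amendment. Enrollment has begun (*Trial status*), so dates for patients already discharged before day 28 would have to be obtained retrospectively. No treatment changes.
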